### **3.3 What are the planned trial interventions.**

**Infection control website.** Our key intervention will be access with a personal password to a website providing advice on infection control behaviours, with reinforcement by email reminders to use the site. A website is likely to be the most efficient and cost-effective mode of delivery in a pandemic as the majority of homes now have access to the web and the figure rises each year (National Statistics; August 2006); currently more than 60% of households have access to the web and the figure goes up year on year by 5% each year in a linear fashion - which suggests that even by the end of this trial 80-90% of families could have home access to the web. A recent US study confirmed that most people would use Google as their first source of information in a pandemic. A website will facilitate tailoring of the intervention to the individual, and personalised action planning - and thus is the most likely to be effective. Having both personalised advice via the web and behavioural prompts (regular email contacts) will provide mutual reinforcement of consistent messages. The website will be tailored to provide targeted advice based on the factors that have been shown to be important influences on behaviour in the qualitative study and survey carried out in the development phase. These are likely to include: family circumstances and lifestyle factors that may affect which behaviours are feasible and preferred (e.g. availability of suitable space to isolate infected family members, skincare problems); beliefs and concerns regarding infection transmission and control; strategies for overcoming barriers to adherence (e.g. forgetting, negotiation with other family members); current infection status of family and adherence levels (i.e. specific advice will be given when the individual or another member of the family is ill, and depending on the current level of reported adherence to each behaviour). The randomised individual (the index person) will be the main target for behaviour change which should limit spread from that person to members of the household and vice versa. However the maximum effect on illness in the family will be if all members of the household participate and change behaviour; this will be encouraged at invitation, and all members of the household will be encouraged to use the website. The extent to which it is possible to engage other members of the household, and the optimum methods for achieving this will be explored in the development phase. During the pilot, participants will be made aware that they will not be able to participate if all other members of their household refuse to provide additional information on their cold and flu illnesses. Through the website and the individual passwords

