**Theoretical basis.** The behavioural literature and empirical trial data suggest that a tailoring approach that personalises advice to the individual is likely to be most effective in changing attitudes and behaviours. Psychological theory will be used to identify the factors on which advice must be tailored. The Theory of Planned Behaviour will be used as the primary basis for developing the tailored intervention, as there is evidence that components of the model that are amenable to change by intervention are key predictors of health-related behaviour; a meta-analysis of 47 studies also shows that these attitudes/beliefs can be experimentally manipulated and do then change behaviour. We have experience of several successful studies which have used structured booklets based on the Theory of Planned Behaviour combined with traditional behavioural techniques. The Theory of Planned Behaviour identifies the proximal factors influencing behaviour (perceived costs/benefits, others' attitudes, barriers/support). To investigate additional factors that may directly or indirectly influence behaviour it can be useful to draw on more than one theory; for example, the Theory of Planned Behaviour can be usefully supplemented by Self-Regulation Theory and by considering volitional factors influencing the implementation of intentions. We will therefore employ a causal modelling approach to identify additional relevant influences on behaviour and appropriate corresponding methods of intervening to change behaviour. We will use Protection Motivation Theory to look at perceived threat of infection (personal vulnerability, consequences, and fear), since mask-wearing in the SARS epidemic was related to perceived susceptibility to infection as well as perceived benefits of mask-wearing. We will use the Self-Regulatory Model to examine personal models of viral infection (e.g. perceived cause, nature and timeline of infection) that may affect attitudes to infection control (e.g. beliefs that respiratory infection is entirely airborne or occurs too quickly to be prevented), as there is limited evidence that these may have influenced behaviour during the SARS epidemic. We are aware of no theoretical work on factors influencing our target behaviours in the context of nonpandemic respiratory infection. However, based on the literature on behaviour to limit STD transmission we will assume that infection control will require negotiation between the patient and other family members. We will also use evidence-based methods of assisting patients to carry out their intentions regarding preventive behaviour including: a) planning and cueing of behaviour, for example assisting the individual to set their own behavioural 'targets' for different infection control behaviours, and to make an explicit commitment to these targets (a signed list and website record), where possible in collaboration with members of their family; b) identifying situations when lapses may occur, and suggesting coping strategies; c) using a paper or web-based diary to self-monitor the target behaviours during episodes of RTI ( this will automatically trigger reinforcement and advice relevant to self-reported behaviour).

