
**3.5 Methods of protecting against bias (e.g. masking, blinding)?** Blinding of patients to whether they have

received the intervention is impossible. Data entry will be blind to study group. Selection bias and non-response/loss to follow-up bias will be assessed by comparing the socio-demographic/clinical characteristics of those recruited/not recruited and followed up/not followed-up respectively. **Selection bias:** We will document when eligible patients are not entered into the study, the reason why, treatment, and clinical characteristics.

**3.6 Inclusion criteria.** Adult patients (aged 18+) from GPs computerised lists where there is at least another living in the household. **Exclusion criteria.** Patients with severe mental problems (e.g. major uncontrolled depression/schizophrenia;dementia;severe mental impairment - unable to complete outcomes) or terminally ill. Patients who have reported a skin complaints that may affect their ability to wash their hands. Participants who live in a household where no one else is willing to provide information on illnesses via the website.

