### 3.7 What is the proposed duration of treatment (see interventions)

### 3.9 and 3.10. What are the proposed outcome measures, frequency and duration of follow-up?

- **Primary: Episodes of ILI and RTI, their duration and transmission in families.:** *We hypothesize that the intervention will reduce the number of episodes (by reducing transmission) and hence the number of days with symptoms.* During the feasibility phase we will pilot the use of both paper and web versions of illness diaries, and of monthly questionnaires (both web and paper based) with emailed reminders. Our preference is that index patients will be prompted by email to log onto the website monthly to complete questionnaires about illnesses during the last month since the duration of symptoms can be remembered reliably over a period of a few weeks. However those that prefer will be provided with a double sided A4 sheet (and spare sheets in case of families with frequent infections) to provide simple summary diary entries of respiratory tract infection, and will still get the monthly email prompt reminders. For each episode the index person will document: the nature of the infection; the duration of symptoms rated moderately bad (which we have shown is the most likely to be sensitive to change for individuals with cough and fever and can be remembered reliably over a period of a few weeks); the number of days where work/normal activities were impaired; whether other family members either had a similar infection before or after the index case, and what the time interval was; whether contact with the health service was needed; and (for the intervention group only) how well the index patient and other family members complied with the target behaviours. We have used diary sheets in our respiratory studies and found good levels of compliance. The monthly illness information will be supplemented by a questionnaire at the end of the winter (April) documenting the summary information, and which can be validated against the monthly information. We are currently using a similar end of winter questionnaire in a study of respiratory and ear infections in families (the 'PIPO' study <http://www.controlled-trials.com/ISRCTN53286030>), and shown it to be feasible and reliable; this questionnaire will particularly provide some information for those individuals not returning their diary or monthly questionnaires. Our experience with questionnaires is supported by illness transmission studies where similar questionnaires/diaries have been used. An illness will be classified based on the records as a potential ILI based on reported fever (or measured temperature >37.5), plus a respiratory symptom (sore throat, cough, coryza) plus a systemic symptom (prostration, headache, severe fatigue, severe muscle aches, severe malaise) i.e. using an analogous definition to the diagnostic sub-study. We will base our definition of RTI on consensus definitions developed in previous studies - which have defined a respiratory tract infection as 2 symptoms of an RTI for at least 1 day or 1 symptom for 2 consecutive days. Evidence of transmission will be defined as a respiratory illness developing within a week of another family member (viral shedding occurs mostly in the 5 days after symptoms commence and the average incubation period is 2 days). We will assess the implications of using different cut-offs in defining both symptomatic RTIs and the time defining transmission of RTIs.

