used in previous studies, including the MRC ATEAM trial, and two vertigo trials. To reduce social desirability effects on reporting of adherence, the PETS asks patients to what extent they have been prevented from carrying out the intervention by socially acceptable reasons (e.g. symptoms too severe or aggravated by the intervention; doubts about efficacy; uncertainty about how to carry out the intervention; practical problems such as lack of time or opportunity, forgetting). They are only then asked how often and over how many weeks/months they adhered to each aspect of the intervention. To compare the effects of the intervention as a whole with the effects of the website and the target behaviours, in addition to the main intention-to-treat analysis we will carry out per protocol analyses to determine the effectiveness of the intervention in a) those who logged on to the website and b) those who reported adhering to each of the different target behaviours. We will also examine whether the website was equally effective for all sections of the target population (based on age, sex, family factors, deprivation). For the purpose of these analyses, we will supplement and validate the PETS scores using the prospective records from the web-based diary of compliance to the behaviours in each episode of family respiratory illness (completed by the intervention group only).

- **Socio-demographic and comorbidity data.** We will collect age, gender, social indices based on post code (to calculate the index of material deprivation), co-morbidities from the notes where available, and educational level from the patient. This data will document the generalisability of the sample, the similarity of trial groups, and explore effect modification due to deprivation or other demographic variables (although we did not find effect modification previously). The issue of deprivation is relevant since currently 25% of those without web access cite costs of equipment or cost of access as a contributory factor to limiting access. We will document how deprivation (measured by the index of material deprivation based on post code) relates both to uptake and effectiveness of the intervention.

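### The per-episode record behind the self-reported primary outcome carries a compliance item in the intervention arm only, which could bias this unblinded comparison in either direction

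*Protocol*

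**What the plan says.** Protocol sections 3.9 and 3.10 define the primary outcome as "Episodes of ILI and RTI, their duration and transmission in families". The index person supplies it, preferably through a monthly web questionnaire, or on an A4 summary sheet for those who prefer paper. For each episode the listed items include the nature and duration of the illness and "whether other family members either had a similar infection before or after the index case, and what the time interval was". The same list closes with an item asked "for the intervention group only) how well the index patient and other family members complied with the target behaviours".

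The paragraph on attitudes and adherence in the same section confirms the asymmetry. It plans to validate adherence scores against a "web-based diary of compliance to the behaviours in each episode of family respiratory illness (completed by the intervention group only"). Section 3.3 (Theoretical basis) makes a diary part of the intervention: "using a paper or web-based diary to self-monitor the target behaviours during episodes of RTI", with entries setting off reinforcement and advice.

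Section 3.5 says that blinding patients to whether they have "received the intervention is impossible. Data entry will be blind to study group".

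Two other sources bear on the point. An April questionnaire summarises the winter, can be checked against the monthly reports, and fills in for people who did not return them. A group-blind review of GP notes supplies a secondary outcome.

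**The concern.** When patients know their allocation and report the outcome themselves, collecting it identically in both arms is one of the few protections left. Here the record that yields the outcome differs by arm. An intervention patient who reports an illness is also asked how well the household complied; a control patient is not.

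Two opposite effects are plausible. The extra item adds work and may feel like admitting a lapse, which would lower reporting. The protocol itself gives some support for this. Section 3.3 (Pilot trial) notes possible demotivation when people fall ill despite the advice, and the adherence paragraph accepts that such answers are open to social desirability. Against that, keeping a behaviour diary during illness may make episodes better remembered and more fully reported.

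The target differences are 2 to 4 percentage points, so a modest difference in reporting between arms could matter. A larger sample does not remove this kind of bias.

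**Working it through.** **Inputs from the protocol (section 3.12, its table, and 3.15).** Control transmission 20%; targets 16% (ILI) and 18% (all RTI); two-sided 5% level; 80% power; 24% of patients with ILI transmission possible; 20% loss to follow-up; 16,000 randomised. Equal allocation is assumed, since the table gives a single number per group.

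**Reproducing the plan's figures.** With p̄ the mean of the two proportions,

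n = [1.96·√(2p̄(1−p̄)) + 0.8416·√(p₁(1−p₁)+p₂(1−p₂))]² / (p₁−p₂)²

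- 20% vs 16%: n = 1,447 per group, as stated. Total 2 × 1,447 / 0.24 / 0.80 = 15,073 (stated 15,074; rounding).
- 20% vs 18%: n = 6,039 per group, as stated. Total 2 × 6,039 / 0.80 = 15,098, as stated.

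The sample-size arithmetic is not in question.

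**Numbers analysed from 16,000 randomised.**

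- ILI: 16,000 × 0.24 × 0.80 / 2 = 1,536 per arm.
- RTI: 16,000 × 0.80 / 2 = 6,400 per arm.

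**Under-reporting with no true effect.** Let the true rate be 20% in both arms and let a relative fraction u of affected intervention patients go unreported, with denominators held fixed. The protocol gives no value for u; the range below is an assumption. The apparent intervention rate is p₂ = 0.20 × (1 − u). With d = 0.20 − p₂, c = 1.96·√(2p̄(1−p̄)/n) and s = √([p₁(1−p₁)+p₂(1−p₂)]/n), the rejection probability is Φ((d−c)/s) + Φ((−d−c)/s).

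Example, u = 10%, RTI: p₂ = 0.18, p̄ = 0.19, c = 0.01359, s = 0.00693, and (0.02 − 0.01359)/0.00693 = 0.92, so the probability is 0.82.

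| Assumed u | Apparent rates | OR | False-positive rate, ILI (1,536 per arm) | False-positive rate, RTI (6,400 per arm) |
|---|---|---|---|---|
| 0 | 20% vs 20% | 1.00 | 5% | 5% |
| 2% | 20% vs 19.6% | 0.98 | 6% | 9% |
| 5% | 20% vs 19% | 0.94 | 11% | 30% |
| 10% | 20% vs 18% | 0.88 | 29% | 82% |

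**Sensitivity to the unit of omission.** The planned logistic analysis is per index patient. If 10% of transmission events are missed, rather than 10% of affected patients, someone with several events may still count as affected. Under a Poisson assumption, −ln(0.80) = 0.2231 events per person; 0.9 × 0.2231 = 0.2008; 1 − exp(−0.2008) = 18.2%. The RTI false-positive rate is then about 74% rather than 82%.

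**Over-reporting with a true effect.** Take a true 20% vs 16% for ILI with 1,536 per arm, where power is 82%. If the intervention arm reports 5% more, the apparent rate is 0.16 × 1.05 = 16.8% and power is 63%. At 10% more it is 0.16 × 1.10 = 17.6% and power is 40%.

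**The case against.** The asymmetry is deliberate. Section 3.9 and 3.10 limits questionnaires that might change behaviour in controls, and self-reported adherence drives the tailored advice, so it belongs to the intervention. That is a good reason not to ask controls about compliance. It is not a reason to place the item in the outcome record, and separating the two leaves controls unexposed.

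The text adds one clause to a list of shared items. It fixes neither layout nor order, and the mode of collection is left to piloting. This stands: the extra burden may be small. The arm-specific content of the record is nevertheless stated.

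There are partial safeguards. The April questionnaire has no stated arm restriction, but it is a supplement and is also unblinded self-report. The notes review is blind but secondary, and cannot see illnesses that never reached the practice.

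A reader might infer three further things that the documents do not support:

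- That the arm-specific item defeats the promise that "Data entry will be blind to study group". The preferred route is web completion by the patient, and section 3.17-.18 has paper forms scanned. No path from data entry to a biased outcome is shown.
- That because "all members of the household will be encouraged to use the website", household illness reporting exists in the intervention arm only. Section 3.6 excludes, without distinction by arm, anyone whose household has no other member willing to give illness information through the website.
- That the primary outcome is drawn from the intervention diary. The protocol uses that diary for adherence and names the monthly questionnaire or summary sheet for illness.

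**Conclusion.** The point holds as a design weakness. The record that produces an unblinded, self-reported primary outcome differs by arm, and nothing in the protocol makes it the same. The direction of any bias is unknown. It would be tempting to conclude that the design manufactures a benefit, but the documents do not support this: the diary could equally make reporting more complete in the intervention arm and hide a real effect.

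The size is also unknown. With an assumed 5% to 10% relative under-reporting and no true effect, the false-positive rate is about 11% to 29% for ILI and 30% to 82% for RTI. With 10% over-reporting under a true 20% vs 16%, ILI power falls from about 82% to 40%. These figures rest on assumed reporting rates, a 20% control rate, fixed denominators, equal allocation and omission counted per affected patient. They show sensitivity; they do not predict what will happen. The planned sample size is unaffected.

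**What to change.** 1. Collect the primary outcome on an identical illness questionnaire in both arms, on web and on paper. Submit and lock it before any compliance item is shown.
2. Move the intervention-only compliance items to a separate form or to the intervention diary. Keep them tied to periods of household illness, since many target behaviours in section 3.3 apply only then.
3. State in the protocol that primary outcomes come only from the common questionnaire, or from the common April questionnaire where monthly data are missing, and never from the intervention diary.
4. Compare monthly with April reports by arm as a check for differential reporting.

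The cost is a small redesign of the forms, feasible because collection methods are still to be piloted, and compliance data that are linked less directly to each reported episode. The bias inherent in any unblinded self-reported outcome would remain; the change removes only the part that comes from different forms.

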
we will be able to monitor whether patients have used the website, and how often. Patients who have not used the website will be prompted by email to use the site. Following accessing of the website we will generate regular automated emails at monthly intervals as a reminder to use the website; these reminders will enable us to monitor compliance in the intervention group and give targeted advice. We will provide further email prompts to all patients when influenza virus has started circulating in the community. During the development and pilot phase we will examine the acceptability and feasibility of using the website as the main method of interacting with patients for the whole trial process (including outcome data collection), with paper-based reminders only when web-based measures are not completed. In the development phase we will also explore the need to provide supplies of some materials to help in infection control (a handgel dispenser sufficient to cover periods of respiratory illness).

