- **Secondary. Attendance at the GP practice, and use of health service resources: Notes review.** *We hypothesize that the intervention will reduce the number of health service contacts by reducing the number of episodes.* At the end of the study all patients' GP notes will be reviewed to document admission to hospital for respiratory or cardiovascular complications, whether patients attended the GP for their ILI or other respiratory tract infections, whether antibiotics or antivirals were prescribed, and/or any subsequent referrals. Assessment of the notes will be made blind to group, and has been shown to be reliable and unbiased.
- **Attitudes and adherence to infection control behaviours.** *We hypothesize that the intervention will change attitudes, beliefs, intentions, and behaviour.* We will assess attitudes, beliefs, intentions, and self-reported adherence for each behaviour on 7 point Likert scales both in the pilot study (after 1 month and 3 months), and in the main trial at the end of the winter (we will randomly choose 1:20 patients for this outcome). These outcomes will be measured in both groups in the main trial only at the end of the winter, to minimise any effect on behaviour change of administering questionnaires in the control group. These outcomes will allow us to check whether the intervention is successful in effecting change and whether outcomes of the intervention are mediated by changes in these variables. To accompany the winter illness questionnaire we will use an adherence questionnaire (the 'Problematic Experiences of Therapy Scale'; PETS) that we have

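### The log-on, adherence and mediation analyses rest on self-selected or after-the-event measures and cannot support the causal conclusions that the protocol draws from them

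*Protocol*

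**What the plan says.** Protocol sections 3.9 and 3.10 plan three secondary uses of post-randomisation measures, "in addition to the main intention-to-treat analysis".

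- **Log-on.** "we will carry out per protocol analyses to determine the effectiveness of the intervention in a) those who logged on to the website". Section 3.3 says how use is recorded: through individual passwords, "we will be able to monitor whether patients have used the website, and how often". Controls receive access only at the end of the trial.
- **Adherence.** The second per-protocol set is "b) those who reported adhering to each of the different target behaviours". Adherence is taken from the PETS scale, sent with the end-of-winter illness questionnaire. PETS is supplemented and validated by "prospective records from the web-based diary of compliance to the behaviours in each episode of family respiratory illness (completed by the intervention group only"). The subgroup paragraph of section 3.17-.18 also asks whether self-reported adherence to each behaviour determines outcome.
- **Mediation.** Attitudes, beliefs, intentions and self-reported adherence are to show "whether outcomes of the intervention are mediated by changes in these variables". On timing: "These outcomes will be measured in both groups in the main trial only at the end of the winter". On numbers: "we will randomly choose 1:20 patients for this outcome".

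The protocol attaches no caveat about causal interpretation to any of these analyses.

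**The concern.** Randomisation protects a comparison of everyone allocated to the website with everyone allocated to normal care. It does not protect a comparison that starts from what people in one arm chose to do, or from what they said about themselves once the winter's illnesses were over.

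People who log on may be healthier and more careful than those who do not, or may log on because somebody at home is ill. People who report adhering to sickroom measures are largely people who had somebody sick to adhere for. Beliefs about handwashing recorded in April may have been changed by the winter just ended.

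The aim here is to learn whether the website works in its users, which behaviours matter, and by what route. Those answers would shape advice in a pandemic. An ineffective website could appear beneficial or harmful in such analyses, and a belief with no influence on illness could appear to be the mechanism.

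**Working it through.** **The plan's own figure.** Section 3.12 gives 20% vs 16%, two-sided 5%, 80% power, 24% at risk of ILI transmission and 20% loss.

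n = [1.96√(2×0.18×0.82) + 0.8416√(0.20×0.80 + 0.16×0.84)]² / 0.04² = (1.0649 + 0.4566)² / 0.0016 = 1447 per group, as printed. Then 2×1447/0.24/0.80 = 15,073, against 15,074 printed. The risks and at-risk share used below are therefore the protocol's own.

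**Log-on.** Assume a website with no effect, a risk of 20% among those at risk, a log-on share L, and a risk ratio r of users to non-users. Neither L nor r is in the protocol. Non-user risk = 0.20/(L·r + 1 − L); user risk = r times that; odds ratio against all controls = user odds/0.25. For L = 0.5 and r = 0.67: 0.20/0.835 = 0.2395; ×0.67 = 0.1605; (0.1605/0.8395)/0.25 = 0.765.

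| L | r = 0.67 | r = 0.80 | r = 1.25 | r = 1.5 |
|---|---|---|---|---|
| 50% | 0.765 | 0.865 | 1.143 | 1.263 |
| 70% | 0.844 | 0.914 | 1.081 | 1.143 |
| 90% | 0.942 | 0.970 | 1.026 | 1.043 |

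The true odds ratio is 1 in every cell. Both directions are plausible: section 3.3 tailors advice to current illness in the family, which can prompt use, and sections 3.9 and 3.10 prefer outcome questionnaires to be completed on the website.

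**Adherence.** No arithmetic applies; the passages have to be read together. Under the target behaviours in section 3.3, regular handwashing runs all winter. Cleaning surfaces, separate towels and distancing are asked for once someone in the household is ill. The diary is kept per episode and only in the intervention arm. A household with no episode therefore has no diary entry and no occasion for most of the behaviours. PETS is not triggered by an episode, but it is completed after the winter and lists severe symptoms among the reasons for not adhering. Recorded adherence can thus depend on the outcome it is meant to explain.

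**Mediation: size.** 16,000/20 = 800; ×0.80 = 640; ×0.24 = 153.6, or 76.8 per arm.

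- ILI transmission, 20% vs 16%: power = Φ[(0.04 − 1.96√(2×0.18×0.82/76.8)) / √((0.16 + 0.1344)/76.8)] = Φ[(0.04 − 0.1215)/0.0619] = Φ(−1.32) = 9%. The full trial has 16,000×0.80×0.24/2 = 1536 per arm and 82%.
- All RTIs, 320 per arm, 20% vs 18%: 9% by the same formula.
- Days of illness, standardised effect 0.15, two-sided 1%: Φ(0.15√(320/2) − 2.576) = Φ(−0.68) = 25%.

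These are powers for the total effect, before any attempt to split it.

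**Mediation: time order.** Assume beliefs have no effect on illness, the intervention raises the belief score by 0.3 SD, the total odds ratio is 0.762, and illness shifts the end-of-winter score by d SD. For a normal score with unit SD, regressing illness on arm and score gives an odds ratio of exp(d) per SD of belief and 0.762×exp(−0.3d) for arm.

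| d | OR per SD of belief (truth 1) | 'Direct' OR for arm (truth 0.76) |
|---|---|---|
| +0.2 | 1.22 | 0.72 |
| +0.4 | 1.49 | 0.68 |
| −0.2 | 0.82 | 0.81 |

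A simulation of 1,000,000 patients agreed to within 0.01. The last row looks like partial mediation, although there is none.

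**A log-on estimate that respects randomisation.** Whole-arm ILI transmission is 0.24×20% = 4.80% vs 0.24×16% = 3.84%, a difference of 0.96 points. Divided by an assumed log-on share of 70%, this is 0.96/0.7 = 1.4 points among those who would log on; 0.96/0.9 = 1.1 and 0.96/0.5 = 1.9 give the range.

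**The case against.** **These are secondary analyses.** Section 3.3 speaks of exploring component effects, and section 3.17-.18 places adherence among subgroup analyses at the 1% level. This stands: the primary result is untouched.

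**The log-on comparator is not stated**, and an analysis plan could choose a sound estimator from data already collected. This stands in part. The log-on table above is an illustration of one natural comparison, not a reading of the plan. But the protocol itself commits to a per-protocol analysis in a self-selected subset that cannot be identified among controls.

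**The diary only supplements PETS, and handwashing, the emphasised behaviour, does not depend on illness.** Both are true. They limit the adherence point without removing it, because the other behaviours do depend on illness and PETS is still retrospective.

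**Measuring beliefs once was deliberate**, to avoid questionnaires changing behaviour in controls. That is a legitimate reason. Nor is a missing baseline fatal for comparing the arms, since randomised groups can be compared on end-of-winter levels. Neither argument puts the mediator before the outcome.

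Two stronger readings are tempting and fail:

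- A reader might infer that log-on, too, is recorded after or because of the outcome. Section 3.3 records it prospectively by password; the fault there is self-selection.
- A reader might set 20% transmission in affected homes against 4.8% in the whole control arm and infer a large built-in excess among diary-keepers. That mixes denominators. Among those at risk, the base used in the section 3.12 table, the control rate is also 20%. The diary also covers every family respiratory illness, not only ILI.

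**Conclusion.** The concern holds for interpretation. The log-on analysis is open to selection bias of unknown direction. The adherence analyses can be conditioned on the outcome. The mediation analysis has its mediator measured after the outcome, without a change score, in a sample with about 9% power for the total ILI effect. For adherence and beliefs, a later analysis plan cannot repair this, because the protocol fixes when the data are collected.

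The sizes of bias rest on assumed inputs: log-on of 50-90%, user risk ratios of 0.67-1.5, and belief shifts of −0.2 to +0.4 SD. They show what can happen, not what will. The timing point takes the winter's illnesses as the outcome. Follow-up lasts a year and may include later events, but the protocol does not tie mediation to those.

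**What to change.** **Log-on.** Replace the per-protocol analysis with a complier average causal effect in all randomised patients, with allocation as the instrument. Define receipt as log-on to the intervention pages, so that completing outcome questionnaires does not count. Controls have no access during the trial, so the risk difference is the intention-to-treat difference divided by the log-on proportion, both on the whole-arm denominator. The 4-point target applies only within the 24% at risk and should not be divided by a whole-arm log-on share. Cost: analysis wording only. Downside: it assumes that allocation acts only through log-on, which email prompts or the invitation alone could breach.

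**Adherence.** Report these results, including the item in section 3.17-.18, as observational associations. Remove the claim that they determine effectiveness for each behaviour, and do not define adherence from the episode diary. Cost: wording only.

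**Beliefs.** Limit the main-trial belief data to a between-arm comparison of end-of-winter levels, and delete the mediation claim or label it exploratory. Measuring beliefs at 1-3 months in the 1:20 sample, as the pilot does at 1 and 3 months, and relating them to later illness would restore the time order. It is an option only if the sponsor accepts questionnaire reactivity in that 5% of patients, and it would not cure the small numbers.
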